### Data collection

#### PAR-Q and anamnesis

Firstly, following what is put for people aged between 15 and 69 in the State of São Paulo Law No. 16724 of 22 May 2018, participants will answer the Physical Activity Readiness Questionnaire (PAR-Q) and those who respond positively to any of the questions, they will sign the Term of Responsibility.

Sociodemographic data, general, and specific (COVID-19) health status related to lifestyle, information on comorbidity, and drug treatment will be assessed through the Anamnesis. Answers about the symptoms associated with COVID-19 will allow assessing the intensity of the disease’s manifestation.

### Longitudinal responses

#### Questionnaires

The International Physical Activity Questionnaire (IPAQ) - short version, validated in Brazil [43], will measure the usual level of physical activity and the Food Consumption Markers Form of the Ministry of Health [44] to assess food consumption. Participants will be instructed to maintain similar physical activity and eating habits throughout the study. The objective is to certify that the possible differences between the groups after the intervention in the variables of interest are related to the physical training intervention’s effect, not to other environmental factors.

The 12-Item Health Survey (SF-12) will assess the perception of the quality of life [45]. In addition, mental health status will be assessed using the Depression, Anxiety and Stress Scale (DASS - 21) [46], and the calculation of the score will be based on a previous study [47].

#### Autonomic parameters

HR variability (HRV) will be analyzed using the RR intervals (RR) from the Polar Team2 HR transmitter (Polar Electro Oy, Kempele, Finland) and recorded at a sampling frequency of 1000Hz. The data will be recorded and stored for further analysis. The HRV analyses will be performed using custom computer software (CardioSeries v2.0, http://sites.google.com/site/cardioseries) developed by [name] of the University of São Paulo, Brazil. The interpolated RR series will be divided into half-overlapping sets of 256 data points, overlapping 50% (Welch Protocol). The stationary segment will be visually inspected, and those with artifacts or transients will be excluded. Each RR static segment will be submitted to the Fast Fourier Transform (FFT) spectral analysis after the Hanning window [48]. The analysis of HRV will be performed by linear methods and analyzed in the domains of time (SDNN and RMSSD) and frequency (LF, HF, and LF/HF ratio) [49].

#### Anthropometric measurements

The body mass index (BMI) will be used to measure nutritional status recommended by WHO [50], and waist circumference (WC) [51] will also be measured.

#### Body composition

The dual-energy X-ray absorptiometry technique (iDXA - GE Lunar - DPX-NT) will be used to analyze body composition and the distribution of the lean, bone, and adipose tissue. The radiation dose that the participants will receive will be less than 0.05 [52], equivalent to 50 times less than an X-ray exam. When positioned on the device, the subjects will remain immobile in the supine position during the exam (about 15 min). The method will estimate body composition by dividing the body into three anatomical compartments: fat-free mass, fat mass, and bone mineral content.

#### Lung function

For pulmonary function evaluation, a portable spirometer (Micro Medical, Rochester, UK) will be used, following the current standards [53] and guidelines for pulmonary function tests [54]. Participants will be instructed to perform the manoeuvers to assess forced vital capacity (FVC) and forced expiratory volume (FEV).

#### Genotyping

Blood collection will be performed by peripheral venous access after an 8-h fast, and the DNA extraction process adopted will be Salting Out. The ECA I/D genetic variants (rs1799752) will be amplified by polymerase chain reaction (PCR) (Applied Biosystems StepOnePlus), according to a previous study [55]. In addition, the genetic variants of AGTR1 A1166C (rs5186), T>G in the EPO gene promoter region (rs1617640), and G6002A at the EPO receptor (rs121918116) will be determined by real-time polymerase chain reaction (qPCR). The reaction will be performed using an allelic discrimination assay TaqMan (CAH5I790 Thermo Fisher, USA) and TaqMan genotyping master mix (Applied Biosystems, USA).

#### Hematological parameters

Complete blood cell count, such as total erythrocyte count, hematocrit, hemoglobin concentration, mean corpuscular volume, mean corpuscular hemoglobin, mean corpuscular hemoglobin concentration, total leukocyte, platelet, and reticulocyte count will be evaluated. In addition, total cholesterol, triglycerides, HDL-c, LDL-c, lactate dehydrogenase, and liver enzymes (alanine aminotransferase and aspartate aminotransferase) will also be analyzed. The collection will be carried out at the School of Physical Education and Sport of Ribeirão Preto by a trained and specialized professional. Later, the samples will be sent for analysis at the Clinical Analysis Laboratory of the Faculty of Pharmaceutical Sciences of Ribeirão Preto, according to the technical service’s standard routine and methodology. Aiming to determine the EPO concentration in the plasma samples, the EPO Immunoassay ELISA Kit (R&D Systems, Billings, USA) will be used.

#### Dosage of inflammatory soluble protein mediators

The quantification of cytokines IL-6, IL-8, IL-10, and TNF-α will be performed by the ELISA - multiplex method according to the manufacturer’s specifications (R&D Systems, Billings, USA).

#### Inflammatory lipid mediators

The profile of eicosanoids will be evaluated in plasma by mass spectrometry (LC-MS/MS) in samples collected with EDTA anticoagulant at the facility available from the Faculty of Pharmaceutical Sciences of Ribeirão Preto - USP. The standard protocol requires the use of lipid solid-phase extraction and high-resolution multiple-reaction monitoring to develop a target bioanalytical method for eicosanoid quantification. Data acquisition and processing will be performed using PeakView^TM^ and MultiQuant^TM^ software (Sciex, Foster, CA, USA) (Sorgi CA, et al., Scientific Data, 2018).

#### Blood pressure

Blood pressure will be assessed using an automatic digital arm pressure meter (OMRON, model HEM-7113), following the “VII Brazilian Guidelines on Hypertension” [56].

### Physical fitness

#### Maximum aerobic power (VO_2_peak), anaerobic threshold (AT), and exercise intensity corresponding to VO_2_peak (iVO_2_peak)

An incremental test will be used to estimate AT, VO_2_peak, and iVO_2_peak. The warm-up will be 5 min in the mechanical cycle ergometer label *Monark* (Monark, Brazil) without load (0 Kp). At each 2-min stage, there will be an increase of 0.25 Kp (approximately 13 W) until voluntary exhaustion [27]. O_2_ consumption will be measured with each breath using the gas analyzer (K4b^2^, COSMED, Italy), calibrated according to the manufacturer’s specifications. Blood samples (25 μL) will be collected from the earlobe at each stage’s end to analyze the blood [La-]. Concomitantly, HR and RPE will be monitored at the end of each stage. VO_2_peak will be defined as the highest mean VO_2_ in the last 60 s in the test, considering at least three of the criteria: volitional exhaustion, blood [La-] ≥ 8.0 mmol, > 90% of the maximum HR predicted for age (HRmax = 220 - age), RPE ≥ 9, respiratory quotient ≥ 1.10, and inability to maintain a frequency of at least 60 rpm. The iVO_2_peak will be the lowest intensity at which the individual reaches VO_2_peak during the test. If the individual does not sustain the intensity until the stage’s end, the iVO_2_peak will be assumed like peak power (PP), estimated by the equation [57]:
$$ PP= Last\ full\ intensity+\left(\frac{Dwell\ time\  at\  last\ intensity}{Time\ of\ each\ stage}\right)\ast Increment $$

The points obtained between the blood [La-] and intensities will be subjected to two linear adjustments so that the intersection will be assumed as the intensity of AT [58].

A partial evaluation containing the incremental test will be carried out at week 5 (half of the intervention) to adjust the training load (evaluation 2). Therefore, the incremental test will be performed in four moments: evaluation 1 (week 0 - pre), evaluation 2 (week 5 - half of the intervention), evaluation 3 (week 9 - post), and evaluation 4 (week 13 - four after the intervention’s end).

#### Strength resistance of lower limbs and agility and dynamic balance

Three motor tests will be performed in the following order to assess: (i) strengh resistance of lower limbs [59], (ii) agility and dynamic balance [60], and a (iii) 6-min walk [59].

### Statistical analysis

After double data entry, an exploratory analysis of the data will be carried out. The primary objective will be to summarize the values, organize, and describe the data through tables with descriptive measures and graphs. Continuous variables will be expressed in terms of basic descriptive statistics (mean, median, and standard deviation), whereas categorical variables will be described in terms of frequency and percentage. The effects of the different types of training (hypoxia and normoxia), before, after 8 weeks, and after 4 weeks after the intervention, for continuous outcomes will be compared using a linear regression model with mixed effects (fixed and random). If there are binary outcomes, a cox proportional hazards model will be used to estimate the incidence rates and their respective confidence intervals, including potential confounders as covariates. The possible associations between hematological, immunological, autonomic, aerobic, and anaerobic variables will be verified with hypothesis testing and the use of other regression models. In the case of handling missing data, we will use statistical methods as multiple imputation or Bayesian methods. The level of significance will be set at 5% in all analyses.

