### Sample size

For sample size estimation for clinical trial study design, using sample size estimation as comparing parallels groups (such as three training groups: (a) T_H_:R_H_, (b) T_N_:R_H_, (c) T_N_:R_N_), and control group. A power function of 80% will be used, a level of significance of 5% and an average difference between groups of 10% will be estimated. Based on the formula described previously [40], the sample size required per group is 20. Hence, the total sample size required is 80 for the four groups, considering a drop-out rate of 10%, so the total sample size required is 88, that is, 22 individuals in each group [41].

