### Recruitment

The invitation will be made to the Health Institutions to offer the possibility of participating in this research to patients who have had moderate to severe symptoms approximately 30 days after the recovery of clinical signs or medical discharge (hospitalized people). Furthermore, the disclosure will happen for the entire population of Ribeirão Preto, SP, Brazil, and the region through the local television channels, USP’s local radio and news from the internet, social networks, and among other media outlets. Participants will be asked to complete the evaluations on week 0. After that, they will be assigned randomly to each group. This study will develop every effort to control confounding variables. Randomization and allocation will be performed by the research coordinator. Considering special randomization techniques, in this project, we will be using the randomization of matched pairs [42], considering a baseline pairing strategy regarding confounding variables such as sex, age, and level of physical conditioning of the participants for their selection and random assignment in the research groups. As there are three training groups, (a) T_H_:R_H_, (b) T_N_:R_H_, and (c) T_N_:R_N_, pairing groups will be organized consisting of participants based on the matching characteristics above, which will be drawn randomly using Microsoft Excel for allocation to groups. This method is satisfactory and suitable for intervention studies in which there are not many participants. In terms of blinding, only the research coordinator is aware of the allocation. Different researchers will work on the intervention and collect information from the participants as evaluations, who will be blinded to avoid potential bias. To maintain the overall quality and legitimacy of the clinical trial, unblinding should occur only in exceptional circumstances when knowledge of the actual treatment is essential for further management of the patient.

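### The mixed model for VO2peak does not state that it includes the matched sets, the matching variables or baseline as a covariate, so precision available from the design may be forgone

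*Protocol article*

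**What the plan says.** **Randomisation.** The Recruitment section describes matched randomisation, "considering a baseline pairing strategy regarding confounding variables such as sex, age, and level of physical conditioning of the participants". Matching groups are formed on these characteristics and the three training arms are drawn at random within them. The control group is not part of this draw: Design and setting fills it with people who are unavailable for the intervention.

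**Analysis.** The Statistical analysis section says that the types of training, at baseline, after 8 weeks and 4 weeks after the intervention, "for continuous outcomes will be compared using a linear regression model with mixed effects (fixed and random". No fixed or random term is listed. Covariates appear only in the next sentence, which concerns a Cox model for any binary outcomes. VO2peak, the primary outcome, is continuous.

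**Sample size.** The calculation is made "using sample size estimation as comparing parallels groups", with no allowance for matching or covariates. "A power function of 80% will be used", and "an average difference between groups of 10% will be estimated". The result is 20 per group, raised to 88 in total for dropout.

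**The concern.** When arms are drawn within matched sets, members of a set tend to resemble one another and part of the outcome variance is shared between the arms. An analysis without the set leaves that shared variance in the error term. The reported standard error is then larger than the true one, tests reject too rarely under the null, and power is lower than the design could give.

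The contrasts affected are those among the three randomised arms: hypoxia against normoxia, and recovery-only hypoxia against hypoxia throughout. With about 20 per arm and 84 participants already included (Trial status), the analysis is the main place left to gain precision.

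A second loss concerns baseline. A group-by-time model that treats the baseline value as one more repeated outcome yields a change-from-baseline contrast, which is less precise than one that takes baseline as a covariate.

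**Working it through.** **1. The plan's own figure.** "Based on the formula described previously [40], the sample size required per group is 20", but no SD is given and the scale of the 10% is not defined. Reading it as 10% of the mean, with two-sided 5% and 80% power, n = 20 implies

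SD = 10 / [√(2/20) × (1.960 + 0.842)] = 10 / 0.886 = 11.29% of the mean,

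a standardised difference of 0.886. The figure cannot be reproduced independently: an SD of 10% gives 16 per group, 15% gives 36 and 20% gives 63. The dropout step is 80 × 1.10 = 88 (80/0.9 gives 89, an immaterial difference).

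**2. A single post-training measurement, sets left out.** With within-set correlation ρ (assumed), n = 20 and SD = 11.29:

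- reported SE = SD × √(2/n) = 3.57; true SE = 3.57 × √(1 − ρ); ratio = 1/√(1 − ρ)
- type I error = 2 × [1 − Φ(1.96/√(1 − ρ))]
- power without sets = 1 − Φ[(1.96 × reported SE − 10)/true SE]

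| ρ | SE ratio | Type I error | Power, sets left out | Power, sets modelled |
|---|---|---|---|---|
| 0.1 | 1.05 | 0.039 | 0.81 | 0.84 |
| 0.3 | 1.20 | 0.019 | 0.84 | 0.92 |
| 0.5 | 1.41 | 0.006 | 0.88 | 0.98 |

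At this implied effect, power stays above 80% even with the sets left out.

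**3. Baseline in the model, which is closer to the plan.** Simulation of 20 matched triplets, 1,500 runs per setting, outcome in SD units, contrast between two of the three arms. Assumed inputs: ρ (within-set correlation of level), r (pre–post correlation) and λ (within-set correlation of change). The change model stands in for a group-by-time contrast. Arrows run from sets left out to sets modelled; power is at an effect of 0.5 SD.

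| ρ | r | λ | Change: SE | Ratio | Power | Baseline-adjusted: SE | Ratio | Power |
|---|---|---|---|---|---|---|---|---|
| 0.3 | 0.8 | 0 | 0.198→0.198 | 1.00 | 0.678→0.676 | 0.189→0.186 | 1.02 | 0.733→0.744 |
| 0.5 | 0.8 | 0 | 0.199→0.198 | 1.01 | 0.687→0.674 | 0.189→0.180 | 1.05 | 0.737→0.763 |
| 0.5 | 0.8 | 0.1 | 0.200→0.189 | 1.06 | 0.703→0.737 | 0.190→0.173 | 1.10 | 0.745→0.795 |
| 0.5 | 0.8 | 0.2 | 0.199→0.177 | 1.12 | 0.710→0.773 | 0.189→0.164 | 1.15 | 0.763→0.837 |
| 0.5 | 0.6 | 0.1 | 0.281→0.266 | 1.06 | 0.409→0.437 | 0.252→0.215 | 1.17 | 0.484→0.598 |
| 0.5 | 0.9 | 0.1 | 0.141→0.133 | 1.06 | 0.944→0.957 | 0.138→0.129 | 1.07 | 0.959→0.962 |

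With sets left out, type I error ran from 0.028 to 0.055, at or below nominal within simulation error (√(0.05 × 0.95/1500) ≈ 0.006). The change ratios at λ = 0.1 and 0.2 agree with 1/√(1 − λ) = 1.05 and 1.12.

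**4. Baseline as covariate against change.** The variance of a change contrast is proportional to 2(1 − r) and that of a baseline-adjusted one to 1 − r², so their ratio is (1 + r)/2: 0.90 at r = 0.8 and 0.85 at r = 0.7. That is 10–15% less variance. It is computed without sets in the model, so it should not simply be multiplied by the ratios in step 3.

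**The case against.** A reader might infer that the mixed model ignores the matching. The text does not say so: it names no term at all, a random effect for the set would fit its wording, and such detail is often left to a statistical analysis plan. That objection stands, so the point is that inclusion is not stated. What remains is that the section does discuss covariates, but attaches them only to binary outcomes, while the comparison it describes for continuous outcomes is training type by time.

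A reader might also infer that power already counted on is lost. The sample size is for parallel groups and takes no credit for matching, so nothing planned is lost. Under the back-solved SD, a post-only analysis without sets keeps power of 0.81–0.88.

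Third, sex, age and fitness strongly affect the level of VO2peak, which suggests a large loss. Because the model includes the baseline measurement, much of that between-person variance may already be removed. This stands too, and is why the relevant size comes from step 3 and not from the 5–41% of step 2. If the sets explain none of the variance in change, adding them gains nothing and costs about a point of power at most in these runs, which is within simulation error.

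**Conclusion.** The design restricts randomisation on three prognostic variables, and the analysis text for the primary outcome does not state that it uses them. If the model is fitted as training type by time with nothing more, the contrasts among the three training arms are valid but conservative. The excess in the standard error is about 0–12% for a change-type contrast and 2–17% with baseline adjustment, or about 0–11 points of power at 0.5 SD. Using baseline as a covariate in place of a change contrast is worth 10–15% of the variance at pre–post correlations of 0.8–0.7.

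All these sizes rest on assumed correlations and an assumed effect, because the protocol gives no SD, within-set correlation or pre–post correlation. This is forgone precision: false positives are not inflated, and the omission does not by itself take power below 80%. Whether 80% is met at all depends on an SD that the protocol does not state.

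The argument covers only the randomised arms. The control group lies outside the matched draw, and there sex, age and fitness matter for confounding as well as for precision.

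**What to change.** For the three randomised arms, state that post-baseline VO2peak is analysed in a mixed model with arm, visit, arm-by-visit, baseline VO2peak, sex and age as fixed effects, and participant and matched set as random effects. Incomplete sets stay in; some are likely, since 10% dropout is expected and the criteria remove people for missed sessions. Week 5 may be included as a visit, but the comparisons after 8 weeks and 4 weeks after the intervention remain the targets. Treat each secondary continuous outcome the same way, with its own baseline.

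For contrasts with the control group, adjust for sex, age and baseline VO2peak, and say that this reduces confounding by measured variables but does not make the comparison randomised.

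The cost is analysis wording, a few degrees of freedom, and a negligible loss of power if the sets explain no residual variance. Sex, age and baseline VO2peak are already available. The protocol does not say that set identifiers from the spreadsheet draw are kept, so the sponsor should confirm that they are and carry them into the analysis dataset.

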### Ethics

This study was approved by the School of Physical Education and Sport of Ribeirão Preto – University of São Paulo (USP) and Faculty of Pharmaceutical Sciences of Ribeirão Preto *–* USP Research Ethics Committees (CAAE: 33783620.6.0000.5659, and CAAE: 33783620.6.3001.5403, respectively). Activities will start after signing the free and informed consent term presented by the coordinator of the study. Following the Research Ethics Committee orientations, a biorepository at the School of Physical Education and Sport of Ribeirão Preto *–* USP was created to store biological samples for use in future studies depending on the participants consent (CAAE: 33783620.6.0000.5659).

All care for the safety of the participants and the work team will be taken. First, an evaluation of the health status will be carried out. The participants who do not have limitations or discomfort that may prevent the evaluations’ performance or the intervention will participate in the proposed intervention. Data will be added to a confidential dataset, and an alphanumeric code will be assigned to each participant. All local databases will be secured with password-protected access systems.

Any modifications to the protocol which may impact on the study conduction, the potential benefit of the participant or safety, including changes of study objectives, design, procedures, participant population, sample sizes, or significant administrative aspects will require a formal amendment to the protocol and will be communicated to the Brazilian Clinical Trials Registry (RBR-5d7hkv) and the Research Ethics Committees.

Authors will create scientific reports to be submitted to peer-reviewed journals. Also, information about the different outcomes will be shared in different scientific events.

## Discussion

It is plausible that the convalescent people of COVID-19 who showed moderate to severe symptoms are in the process of gradual recovery and still have changes in their health status, even after approximately 30 days of recovery from clinical signs or medical discharge. Therefore, the monitoring control group that will not train will describe the effects of COVID-19 on lung function, hematological, immunological, autonomic parameters, physical fitness, and mental health.

The gradual recovery process of the participants will be observed according to the association of training (T) and recovery (R) with hypoxia (H) or normoxia (N). Therefore, it is expected that the normoxia training and recovery group (T_N_:R_N_) can show better results compared to the control group. Besides, both groups that will train in hypoxia may demonstrate even better results than the T_N_:R_N_ group, with a higher result for the group that will perform the training in normoxia and the recovery in hypoxia (T_N_:R_H_), comparing the group that will perform training and recovery in hypoxia (T_H_:R_H_). The justification for these two groups to train differently associated with hypoxia is that exercise intensity can be reduced with hypoxia exposure. In this way, to minimize this possibility, the group that will breathe hypoxia air only during the pause could perform the training stimulus in greater intensity (normoxia).

The expectation is that physical activity can be used to face the COVID-19 pandemic and other health problems as a complementary treatment. The consolidated evidence on the benefits of physical activity for physical, physiological, social, and mental health and the knowledge generated by this research project may contribute to solving priority health problems in Brazil. Furthermore, this project’s results may contribute to the qualification of health care practices and promote scientific, technological, and innovation development in the Health area, aiming at strengthening the Unified Health System of Brazil.

Still, it is expected that the genetic variants studied may be associated with the recovery process of the convalescents of COVID-19 and with the effect of moderate training combined with intermittent normobaric hypoxia. The study of genetic variants can bring important advances in understanding the variation in responses related to the triggering and progression of some diseases and the effect of physical training.

To improve retention, we will provide (i) written feedback to all participants about the assessments results at the beginning, after 4, 8, and 12 weeks of the intervention; (ii) periodic communications and presentations to inform the current status of the study, plans for the next phase, and motivating the participation; and (iii) flexible as possible with training sessions and evaluations schedule.

Accessing participants can be difficult due to the social isolation imposed by the pandemic. However, this limitation can be minimized by emphasizing the benefits that the intervention proposed by the present study can promote and emphasizing that all safety-related care will be taken.

The pandemic caused by the SARS-CoV2 virus is not yet under control, and the state of global emergency in Public Health remains declared. The number of deaths and new cases remains high. Even though the recovery rate is high, changes are observed in recovered patients even after 30 days of the interruption of clinical signs or medical discharge, in addition to some undeclared sequelae. Thus, a moderate-intensity interval training program performed in intermittent normobaric hypoxia could be an efficient alternative in rehabilitating convalescents who presented moderate to severe symptoms to recover lung function, physical fitness, quality of life, and mental health, as well as immunological homeostasis, preventing chronic and autoimmune inflammatory diseases, and preventing new infections. And the study of genetic variants can provide important advances in a better understanding of disease progression variability and proposed treatments.

